### Randomization process and interventions

Eligible patients will be randomized (1:1) into one of the two different study arms (CG, control group/IG, intervention group) using block randomization with randomized block length. The randomization is done stratified by study center using an internet-based tool (URL: www.randomizer.at). The randomization is blinded for the patient, blinding of the attended physician is not possible. All included patients will be treated according to current sepsis guidelines [3, 4]. Pathogen diagnostics in patients of the CG will be done with standard-of-care microbiological analyses followed by optional expert consultations, whereas in patients of the IG, a comprehensive concept of digital precision diagnostics (including NGS-based diagnostics, standard-of-care microbiological analyses, and optional expert consultations) will be provided.

### Description of the used interventions

#### Standard-of-care microbiological analyses

Standard-of-care microbiological analyses of potential pathogens in the different specimens (also including rare pathogens of opportunistic infections in immuno-compromised patients such as *Aspergillus* spp., *Mucorales*, *P. jirovecii*, *C. neoformans*, etc*.*) will be performed according to the usual practice in each participating institution.

#### Data analysis and result communication using next-generation sequencing (NGS)

NGS-based measurements will be performed by Noscendo GmbH (Noscendo GmbH, [name]) in its laboratories at [name]. Transfer of samples to Noscendo GmbH will be performed at room temperature by a medical logistics integrator coordinated by Noscendo GmbH and called on demand. In detail, plasma samples for NGS will be prepared at Noscendo GmbH from cfDNA stabilizing tubes (Cell-Free DNA BCT CE by Streck, La Vista, NE, USA) by centrifugation. Nucleic acids will be isolated from the freshly prepared plasma with the QIAsymphony DSP Circulating DNA Kit (Qiagen, Hilden, Germany) on the QIAsymphony SP instrument. Adequate controls will accompany all laboratory and sequencing procedures. The cfDNA will be quantified with the Qubit 1x dsDNA HS Assay Kit (Thermo Fischer Scientific, MA, USA), and quality will be assessed by the High Sensitivity DNA Kit (HS NGS Fragment Kit (1–6000 bp)) on a 5200 Fragment Analyzer System (Agilent, Santa Clara, CA, USA). DNA library preparation will be performed from 1 ng cfDNA input and DNA libraries will be sequenced using a NextSeq550 (Illumina, San Diego, CA, USA) with 75 bp read length in single end mode. Sequencing depth of the samples will be 25 million single end reads minimum, per sample. Raw sequencing data is subjected to various QC controls comprising, PHRED score filtering, adapter trimming, complexity filtering as well as k-mer-based contamination screening. To pass the quality filter, read quality needs to surpass a Phred score of 20 and achieve a minimal length of 50 bp after quality control. All data generated will be analyzed using Noscendo’s CE-IVD platform DISQVER®. Noscendo’s DISQVER® comprises a curated microbial genome database of over 16.000 microbial species covering more than 1.500 pathogens and can detect bacteria, DNA-viruses, fungi, and parasites in one single assay while differentiating contamination, commensals from infective agents. Results of the DISQVER® test will be made available to the commissioning physician via the digital communications solution of Noscendo (NOS-portal).

#### Facultative expert consultations

In terms of an anti-infective stewardship, facultative expert consultations are available for patients in both study groups. However, they are particularly recommended for patients of the IG group (where results of NGS-based diagnostics are made available to the commissioning physician), if NGS-based digital precision diagnostics and standard-of-care microbiological analyses are contradictory. The characteristics and results of consultations in both groups will be monitored and described in detail in the final publication. Because the involvement of the expert group is possible for all patients, their final effect on patient’s outcome is expected to be comparable between both study groups.

### Participant timeline, data collection, and sample handling

#### Data collection

As part of the study, patients´ baseline data is collected once at the time of sepsis diagnosis (= baseline): patient demographics (e.g., age, sex), date and time of hospital and ICU admission, admission source (e.g., emergency department, outpatient clinic/referral, operating room, post-anesthesia care unit, and other hospital units), major comorbid conditions, immune status (host factors predisposing for an immunodeficiency according to [12]; Supplemental File 2), site of suspected or confirmed infection, antimicrobial course prior to study enrolment, surgery/procedures for suspected site of infection prior to enrolment, and Sequential Organ Failure Assessment (SOFA) score (Supplemental File 3). Clinical data collection is carried out at the time of sepsis diagnosis (= baseline), 3, 7, 14, and 28 days later. All laboratory parameters will be measured according to the local standard. The outcome evaluation takes place 28 days after the onset of sepsis. Clinical data collection during admission will include pertinent laboratory data, use of mechanical ventilation, and antimicrobial/antibiotic therapy including duration of therapy, and date therapy will be initiated and discontinued. Vasoactive drug therapy, renal replacement therapy, surgical and other procedures for diagnosis/treatment of infection, radiological testing for diagnosis/evaluation of potential infection, indwelling vascular access devices, and vital status will also be recorded. Discharge data will include the date of discharge (ICU/IMC, and hospital), discharge destination (general hospital ward, skilled nursing facility, and home), and vital status at discharge (survival/death). Finally, quality of life (QoL) of all participating patients will be assessed at onset, 90 and 180 days after sepsis onset using the VR-36 questionnaire [13].

#### Sample collection and sample handling

Culture-based diagnostics include the guideline compliant collection of 2 blood culture sets (2 x aerobic/2 x anaerobic) at baseline and 3 days later. At the same time, blood samples are obtained for NGS-based pathogen diagnostics. Additional sampling for NGS-based diagnostics can be made up to day 14 after the baseline visit or whenever the attending physician establishes a clinical indication for collecting further blood cultures. Routine microbiological findings from other biological samples (e.g., surgical swabs, drainage secretions, tracheal secretions, tissue samples) are included in the evaluation if these were collected within 3 days before or after the extraction of blood samples for NGS-based diagnostics. The study-related burden on the individual study patient includes a total of 10–20 ml whole blood for NGS-based diagnostics. The minimum total volume, therefore, amounts to the collection of 10 ml whole blood within the first 14 days after the onset of sepsis. The sampling takes place with the collection of the blood cultures or within the framework of the daily routine blood samples, so that no further venous punctures are required. Infection parameters such as procalcitonin (PCT) are also carried out within the framework of daily regular blood collection. The same principle applies to the collection of blood cultures which are routinely obtained as part of standard diagnostics in patients with suspected or proven sepsis. The required blood volume of 40 ml whole blood (each two sets of 2 x aerobic/2 x anaerobic = 4 × 10 ml = 40 ml) therefore does not represent an additional study-related burden. A further burden for the patient regarding invasive procedures or examinations is not expected.

### Outcomes

#### Primary outcomes

*DigiSep* primarily evaluates whether the so-called DOOR-RADAR (Desirability of Outcome Ranking/Response Adjusted for Duration of Antibiotic Risk) score can be significantly improved by application of an additional NGS-based diagnostic concept [14] (Table 2).

**Table 2 Tab2:** Primary and secondary outcomes of *DigiSep*-trial

Outcomes	Data source	Timepoint/frame
Primary outcomes		
DOOR/RADAR score	eCRF	28 days
Secondary outcomes		
Long term mortality	Statutory health insurance data, eCRF	90, 180 days
Degree of organ dysfunction/failure: • Duration of mechanical ventilation • Length of time until shock resolution • Ongoing RRT-dependency	eCRF	28, 90, 180 days
Hospital length of stay	Statutory health insurance data, eCRF	28, 90, 180 days
Cumulative need for anti-infective drugs	Statutory health insurance data, eCRF	28, 90, 180 days
Beginning of a targeted anti-infective treatment regimen	eCRF	28 days
Resource utilization (outpatient and inpatient)	Statutory health insurance data	28, 90, 180 days
Duration and costs of incapacity to work	Statutory health insurance data	28, 90, 180 days
Direct medical costs (outpatient and inpatient)	Statutory health insurance data	28, 90, 180 days
Quality-of-life (QoL)	VR-36 questionnaire	0, 90, 180 days

Abbreviations: *RRT* renal replacement therapy; *QoL* quality of life; *eCRF* electronic case report from; *DOOR/RADAR score* Desirability of Outcome Ranking/Response Adjusted for Duration of Antibiotic Risk score

The DOOR-RADAR score represents a combined clinical endpoint. While the DOOR component reflects the overall clinical outcome (OCO) consisting of intensive/intermediate care unit length of stay (ICU/IMC-LOS), mortality, and RRT-dependent AKI, the RADAR component reflects the duration of anti-infective treatment. Both components are combined to yield the DOOR-RADAR score, which is a numerical value and calculated as follows:
$$ \mathrm{DOOR}-\mathrm{RADAR}\ \mathrm{score}\ \left\{\begin{array}{c}=\mathrm{OCO}+\left[\frac{\mathrm{number}\ \mathrm{of}\ \mathrm{days}\ \mathrm{with}\ \mathrm{anti}-\mathrm{infective}\ \mathrm{treatment}\kern0.5em }{\max .\kern0.5em \mathrm{number}\ \mathrm{of}\ \mathrm{days}\ \mathrm{with}\ \mathrm{anti}-\mathrm{infective}\ \mathrm{treatment}\kern0.5em +1\ \mathrm{day}}\right],\mathrm{if}\ \mathrm{OCO}\le 4\\ {}=5\kern28em ,\mathrm{if}\ \mathrm{OCO}=5\end{array}\right. $$

with the OCO being calculated as

1 point: Survival* + ICU/IMC LOS < 12 days without AKI**

2 points: Survival* + ICU/IMC LOS < 12 days with AKI**

3 points: Survival* + ICU/IMC LOS ≥ 12 days without AKI**

4 points: Survival * + ICU/IMC LOS ≥ 12 days with AKI**

5 points: Death of the patient*

(* at/within 28 days; ** with the need for RRT).

Using the DOOR-RADAR score as primary endpoint, it should be delineated whether a patient of the IG has a higher probability for a lower DOOR-RADAR score compared to a patient of the CG, whose anti-infective treatment is guided by standard of care microbiological analyses only.

#### Secondary outcomes

A detailed description of all secondary outcomes is given in Table 2. As part of secondary outcomes, the cost-effectiveness of the new procedure will be evaluated. It is postulated that the length of hospital stay, long-term mortality, incidence of organ dysfunction/failure, the duration of anti-microbial therapy as well as the costs of complications and outpatient aftercare will be reduced. Moreover, a significant improvement in the QoL of affected patients is expected. A detailed flow chart of all trial specific procedures, assessments, and visits for participants is provided in Fig. 1. In Fig. 2, the timing of each visit as well as the procedures and assessments performed at each visit are displayed.

**Fig. 1 Fig1:**
[figure not shown]
Detailed flow chart of specific procedures, assessments and visits of *DigiSep*-trial

**Fig. 2 Fig2:**
[figure not shown]
Schedule of enrolment, interventions, and assessments (SPIRIT figure)

### Sample size calculation

For sample size calculation, a sophisticated secondary outcome analysis of the following four large sepsis studies of the SepNet Study Group (VISEP [15], MAXSEP [16], HYPRESS [17], and SISPCT [18]) was performed, in which the above described OCO-groups were represented as follows: OCO 1: 33%, OCO 2: 3%, OCO 3: 22%, OCO 4: 14%, and OCO 5: 28%. It is assumed that the anti-infective treatment period in OCO 1 and OCO 2 is 7 days in average, whereas it is prolonged up to 15 days (with a standard deviation of 10 days) in average in OCO 3 and OCO 4. Based on the assumption that the OCO group can be improved by at least 2 stages in 42% of IG patients in parallel to a shortening of the anti-infective treatment by 2 days, this would result in a power of 90% with 180 patients in each of the two study groups (CG, IG), provided that an IG patient has a lower DOOR/RADAR score as compared to a CG patient with a relative effect of *p* = 0.6. Including an additional drop-out rate of 12.5% (and considering these patients as OCO 5) would finally result in an overall sample size of 410 patients (CG: *n* = 205/IG: *n* = 205).

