### Statistical methods

The primary hypothesis will be analyzed using Mann-Whitney *U* test. Primary analysis will include all randomized patients (intention to treat (ITT)-population). Although DOOR/RADAR score values can be calculated reliably, any missing data will be replaced with multiple imputation methods [20]. The imputation model will be based on the variables age, SOFA score at sepsis onset, and survival and furthermore assumes that missing values of the primary endpoint are “missing at random”. Accordingly, missing values can be estimated by relevant co-variables in the imputation model. In order to review the assumptions of the imputation model, sensitivity analyses as well as “best case” and “worst case” scenarios will be performed. Moreover, these cases will be analyzed without the missing variables (complete case analysis). The primary endpoint will additionally be analyzed in a dichotomous way (good vs. bad outcome: e.g., OCO 1 versus OCO 2-5) using a logistic regression model, including group membership (CG, IG) and additional confounders (e.g., age, sex, SOFA score, comorbidities) as co-variates. The primary as well as all secondary endpoints will be presented using descriptive statistical methods. Moreover, 95% confidence intervals as well as descriptive *p* values for the effect estimates will be reported. In addition, mortality at 90 and 180 days will be evaluated using methods for survival-time analyses (Kaplan-Meier, Cox-proportional-Hazards-Regression). Wherever possible, graphs are used for visualization. All statistical tests will be performed using SAS (SAS Institute, Cary, NC). A *p* value of < 0.05 will be considered statistically significant. Detailed information of all statistical methods will be summarized and refined in a detailed statistical analytic plan (SAP).

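### The 205 per arm allows for drop-outs as if they left the analysis, but the same sentence scores them as OCO 5 and the analysis section imputes them; under OCO 5 scoring the stated 90% power would be about 77–87% if the relative effect of 0.6 applies to completers

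*Protocol article*

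**What the plan says.** Protocol article, Sample size calculation:

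- The control distribution is "OCO 1: 33%, OCO 2: 3%, OCO 3: 22%, OCO 4: 14%, and OCO 5: 28"%.
- The planned benefit is that "the OCO group can be improved by at least 2 stages in 42% of IG patients", together with anti-infective treatment 2 days shorter.
- On that basis "this would result in a power of 90% with 180 patients in each of the two study groups", on the condition that "an IG patient has a lower DOOR/RADAR score as compared to a CG patient with a relative effect of" 0.6.
- Drop-out comes last: "Including an additional drop-out rate of 12.5% (and considering these patients as OCO 5"), giving 205 per arm and 410 in total.

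Protocol article, Statistical methods: "The primary hypothesis will be analyzed using Mann-Whitney" U test in all randomized patients, and "any missing data will be replaced with multiple imputation methods". The imputation model uses age, baseline SOFA score and survival and assumes missing at random. Best-case, worst-case and complete-case analyses are added. Scoring drop-outs as OCO 5 is not mentioned there. In the Outcomes section OCO 5 means death within 28 days and carries a fixed score of 5.

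**The concern.** Dividing by one minus the drop-out rate restores the number of evaluable patients. It assumes that drop-outs contribute nothing and that the effect among the rest is unchanged. Scoring drop-outs as OCO 5 does something else: nobody is lost, but the same share of both arms is tied at the worst score, so the effect shrinks. A larger n can offset that, but 1/0.875 is not the right factor.

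Two things are at stake. One is the power figure on which the trial relies. The other is which rule governs the primary endpoint. A patient who withdraws alive counts as a death under the sample size wording and is imputed under the analysis wording. The Discussion says that the statisticians will not be blinded, so this choice should not stay open until the data are in. If OCO 5 scoring were the primary rule, unequal drop-out could also look like a treatment effect.

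**Working it through.** **Inputs.** Relative effect p = 0.6, 180 and 205 per arm, drop-out d = 0.125 and control mortality qC = 0.28, all from Sample size calculation. The significance level is 0.05 (Statistical methods: a p "value of < 0.05 will be considered statistically significant"). Sidedness is not stated. Two-sided is assumed, because it reproduces the plan's figure and one-sided does not (143 per arm).

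**1. The plan's own figure.** Noether's formula for the Mann-Whitney test with 1:1 allocation:

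N = (1.960 + 1.2816)² / (3 × 0.1²) = 350.2 in total, about 176 per arm.

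At 180 per arm, √(3 × 360) × 0.1 = 3.286, and 3.286 − 1.960 = 1.326, so power is 90.8%. The stated 90% reproduces.

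**2. The drop-out step.** 180/0.875 = 205.7, and 205 × 0.875 = 179.4. The stated 205 is the plain inflation, rounded down. With 179 per arm, √(3 × 358) × 0.1 = 3.277 and power is 90.6%. So 205 is adequate if drop-outs are simply not evaluable.

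**3. The relative effect with drop-outs scored OCO 5.** Take one patient from each arm, with qI the mortality among IG completers. Adding the four cases (both complete, only the CG patient drops out, only the IG patient drops out, both drop out):

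p′ = (1−d)² p + d(1−d)(1 − 0.5 qI) + d(1−d)(0.5 qC) + 0.5 d²

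With qI = qC = 0.28: 0.4594 + 0.0941 + 0.0153 + 0.0078 = 0.5766.

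IG mortality is not stated, so three values are used:
- 28%: no mortality difference.
- 16.2% = 28% × 0.58: 42% of OCO 3–5 patients improve.
- 9.6%: 42% of all IG patients improve. That is 0.42/0.64 = 66% of OCO 3–5 patients, spread evenly, so 28% × (1 − 0.656).

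**4. Power at 205 per arm.** z = √(3 × 410) × (p′ − 0.5) − 1.960, where √1230 = 35.07. With the tie correction, the first term is divided by √(1 − w³), where w is the pooled share at score 5.

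| IG deaths | p′ | Power, no tie correction | w | Power, tie correction |
|---|---|---|---|---|
| 28% | 0.577 | 76.6% | 0.370 | 78.7% |
| 16.2% | 0.583 | 82.9% | 0.318 | 84.1% |
| 9.6% | 0.587 | 86.0% | 0.290 | 86.8% |

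With IG mortality at zero, p′ = 0.592 and power is 89.7% (90.1% with ties). Under these conditions 90% is reached only if almost no IG patient dies. For 90% power, the first two rows need about 246 to 299 per arm.

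**5. The fuller planning scenario.** The protocol also gives OCO shares and treatment durations, so the scenario can be simulated directly. Assumptions: 42% of OCO 3–5 patients move up exactly two stages; treatment is 2 days shorter; the SD is 10 days in OCO 3–4 and 3 to 10 days in OCO 1–2, where it is not clearly given; durations are normal or gamma.

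- Before drop-out, the relative effect was 0.604 to 0.625, with power at 180 per arm of 93% to 99%.
- With 12.5% scored OCO 5 at 205 per arm, it was 0.585 to 0.602, with power of 86% to 96%.

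**6. Unequal drop-out, no true effect.** With 10% in IG, 15% in CG and 28% mortality in both, the four terms in the same order are 0.3825 + 0.1161 + 0.0119 + 0.0075 = 0.518. That is 0.018/0.10, nearly a fifth of the planned effect, and applies only under OCO 5 scoring.

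**The case against.** The strongest reply is that the OCO 5 clause is only a cautious planning remark. The analysis is set out in Statistical methods, where missing outcomes are imputed, and a pessimistic planning assumption can sit beside a different primary method. On this view the two sections do not strictly exclude each other, and the trial keeps about 90% power. This largely stands: nothing in Statistical methods scores drop-outs as OCO 5 in the primary test. But the clause is then not reflected in the 205, which makes no allowance for the diluted effect, and the reader cannot tell which rule the sample size serves.

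A second reply is that 0.6 might already include the OCO 5 scoring. The text ties 0.6 to the 180 per arm and adds drop-out afterwards, which points the other way, but it does not say so expressly. The simulation in step 5 also shows that about 90% at 205 per arm with OCO 5 scoring is attainable under some readings of the scenario. Within each of those readings, power still falls below that of 180 evaluable patients per arm.

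Third, the 77% end assumes no mortality difference, whereas a shift of two or more stages would be expected to move some patients out of OCO 5. That is fair: 77% is a lower bound rather than the planned scenario. Lastly, the formula 180/0.875 is inferred, not printed, and would normally round up to 206.

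**Conclusion.** The point holds in a conditional form. The step from 180 to 205 fits drop-outs who leave the analysis. It does not fit the OCO 5 scoring named in the same sentence, and the analysis section names a third treatment, imputation. If OCO 5 scoring were applied, with a relative effect of 0.6 among completers, 12.5% drop-out in each arm and a two-sided 5% test, the relative effect would be about 0.577 to 0.587 and power at 205 per arm about 77–87%.

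A reader might infer that the trial's true power is below 90%. The documents do not support that. The dilution does not arise under the stated imputation, and the raw OCO and duration scenario can give a relative effect above 0.6 and higher power. Nor do they show that drop-out imbalance will bias the primary result, since that needs OCO 5 as the primary rule. What is established is an inconsistency in the primary endpoint's missing-data rule and a power statement that does not match the rule beside it.

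**What to change.** Use one missing-outcome rule in both sections.

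- **Preferred:** delete the OCO 5 clause from the sample size section and keep multiple imputation as the primary method. State that 205 per arm with 12.5% drop-out leaves about 179 evaluable patients per arm, giving about 90% power at a relative effect of 0.6. Name OCO 5 scoring of all missing outcomes as one of the worst-case sensitivity analyses already planned. This is a change of wording in the sample size section and the SAP, with no added patients.
- **If OCO 5 scoring is to be primary:** say so in Statistical methods, state whether 0.6 is before or after that scoring, and restate the power. If before, it is about 77–87% at 205 per arm. The cost is a less favourable power statement or a larger sample.

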### Recruitment process

All adult patients (≥ 18 years) in the participating centers with suspected or proven sepsis/septic shock will be considered for inclusion in this study.

### Data collection methods

All data collected in this trial will be recorded on standardized electronic case report forms (eCRF: REDCap/URL: www.project-redcap.org). The investigators are responsible for full documentation of patient data required by the study protocol and for ensuring that all parts of the eCRFs are filled in correctly.

